Trophic tones will be assessed with isotonic and isometric evaluations of abdominal muscles, gluteus medius, minimus, maximus, and spinal extensors. Evaluation of spinal curve accentuations, inversions, or extensions, especially dorsal and cervical, will be conducted in the sagittal plane to identify alterations in head posture that may affect MIGs, including specific cervical. The postural examination will conclude with neuromotor tests: Fukuda and Romberg tests (simple, monopodalic, and sensitized) will be used to assess general proprioception and balance [57].

This assessment will be followed by specific tests to evaluate how muscle contracture or weakness, cervical stiffness or instability, and poor posture may influence chronic or episodic MIG, focusing on the neck and cervical-dorsal muscles.

(e) Gnathological assessment will be conducted in accordance with the international diagnostic criteria (DC)/TMD [58]. This involves a thorough medical history of the disorders, followed by an examination of two reference axes. AXIS I focuses on identifying isolated muscle pain, condylar-disk dislocations, arthralgia, or degenerative bone changes within the temporomandibular joints, whereas AXIS II explores the psychological factors that influence the progression of the pathology and chronic pain. Participants will undergo a 4-channel surface electromyography (Teethan) examination [59]. The Baiobit motion sensor will also be used to perform cervical ROM [60,61], balance, and gait tests to identify ascending or descending interference factors in TMD.

After the evaluation, participants will be randomly assigned to two groups: the control group (*n* = 100), comprising people with MIG in standard care; and the intervention group (*n* = 100), comprising people with MIG in standard care plus supervised EXE intervention. Only the second group will attend a supervised, mixed EXE intervention (phase 3).

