All statistical analyses will be completed using IBM SPSS^®^ Statistics for Windows version 25.0 (IBM Corp., Armonk, NY, USA).

*Sample Size.* The sample size calculation was based on real-life data regarding the response rate to therapy through PA in people with MIG, specifically focusing on the number of headache days. According to the literature, this approach indicates a decrease of approximately 15–20% relative to baseline data [98]. To determine the number of participants in the intervention and control groups, we referenced various articles on the subject, particularly the work of Krøll et al. [98,99], which indicates that the average difference in the number of headache days is almost 2 days less than the baseline. The standard deviation is estimated to be approximately 50% of the average for both groups. Assuming a 1:1 ratio, with a significance level of 5% and a statistical power of 80%, a sample size of a total of around 200 participants (100 patients per group) will be determined, accounting for an anticipated dropout rate of 30%. The recruitment of this cohort will be scheduled for over 9 months to effectively achieve the desired enrollment.

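### The claim that 100 per group gives 80% power after 30% dropout does not follow from the sample-size paragraph's own inputs

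*Protocol article*

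**What the plan says.** All the inputs stand in the sample-size paragraph of section 2.4:

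- **Relative effect:** the literature on this approach shows "a decrease of approximately 15–20% relative to baseline data".
- **Absolute effect:** "the average difference in the number of headache days is almost 2 days less than the baseline".
- **Spread:** "The standard deviation is estimated to be approximately 50% of the average for both groups".
- **Design:** "Assuming a 1:1 ratio", "with a significance level of 5% and a statistical power of 80" per cent.
- **Result:** a "sample size of a total of around 200 participants (100 patients per group) will be determined, accounting for an anticipated dropout rate of 30" per cent.

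The paragraph gives no baseline mean, no SD in days, no sidedness, no baseline–follow-up correlation and no sample size before dropout.

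Three other statements bear on the point. Section 2.2.2 confirms that 100 per group is the number randomised: "After the evaluation, participants will be randomly assigned to two groups", each of 100. Section 2.4 restricts the analyses to participants with complete data and brings in regression imputation only if dropout exceeds what was projected. The primary model in section 2.4 is a linear mixed model over the 6- and 12-month visits with the baseline monthly frequency as covariate.

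**The concern.** The paragraph presents 100 per group as a number that already absorbs a 30% loss. If so, the remaining 70 per group should give 80% power with the stated effect and spread. They do not appear to. The figure of 100 is instead what a standard two-sample calculation returns before any dropout, at the most favourable of the stated inputs.

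The claim concerns the primary outcome. Dropout at the projected rate does cost power here, because the complete-data rule leaves about 70 per group in the analysis and imputation is not triggered at 30%. Anyone who relies on the stated 80% to judge what the trial can detect would be relying on a figure that the stated inputs do not support.

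**Working it through.** **Assumptions, since the text leaves them open.** The 2 days and the 15–20% describe the same effect; the average in the SD sentence is the baseline mean; the test is two-sided; the comparison is of unadjusted means at one visit; and controls do not change, so the fall from baseline equals the between-group difference.

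**1. Baseline mean and SD.** 2/0.20 = 10.0 and 2/0.15 = 13.3 days. Half of each is 5.0 and 6.67 days. So d = 2/5.0 = 0.40 to 2/6.67 = 0.30.

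**2. Evaluable number per group.** Normal approximation: n = 2(1.960 + 0.842)²/d² = 15.70/d².

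- d = 0.40: 98.1, so 99 (exact t-test 99.1, so 100).
- d = 0.30: 174.4, so 175 (exact t-test 175.4, so 176).

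The plan's figure of 100 is therefore reproduced, but as the evaluable number at a 20% fall. Power with 100 analysed per group and d = 0.40 is 80.4%.

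**3. Adding 30% dropout.** n/(1 − 0.30): 99.1/0.7 = 141.5, so 142; 175.4/0.7 = 250.5, so 251. Rounding the evaluable number up first gives 143 and 252. The requirement is about 142–252 randomised per group, against the stated 100.

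**4. Power with 70 evaluable per group.** Power ≈ Φ(d√(70/2) − 1.960).

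| Fall from baseline | SD (days) | d | Evaluable n per group | Randomised n per group | Power at 70 (t-test) |
|---|---|---|---|---|---|
| 20% | 5.0 | 0.40 | 100 | 142–143 | 65% |
| 17.5% | 5.7 | 0.35 | 130 | 185–186 | 54% |
| 15% | 6.7 | 0.30 | 176 | 251–252 | 42% |

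**5. Detectable difference.** With 70 per group, 80% power needs d = 0.477. That is 0.477 × 5.0 = 2.4 days to 0.477 × 6.67 = 3.2 days.

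**6. Other readings of the SD sentence (two-sided, t-test).**

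| SD is half of | Randomised n per group (20% to 15% fall) | Power at 70 (20% to 15% fall) |
|---|---|---|
| each group's own mean | 117 to 216 | 74% to 48% |
| the mean of both groups | 115 to 215 | 74% to 48% |
| the follow-up mean | 92 to 182 | 84% to 55% |

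Only the last comes near 100, and only at a fall of about 19–20%: at 19% it needs 104 randomised and gives 79% power; at 17.5% it needs 126.

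**7. One-sided 5%.** This is not stated. With SD 5 it needs 78 evaluable and 112 randomised (normal approximation), still above 100. It falls below 100 only if combined with one of the smaller SDs in step 6, at or near the 20% end (for example 92 with each group's own mean).

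**8. Working backwards.** For 70 per group to give 80%, the SD must be at most 2/0.477 = 4.2, so the average at most about 8.4. A 2-day fall is then 2/8.4 = 24%, outside the stated 15–20%. An average of 8.4 is also barely above the entry minimum of 8 attacks per month in section 2.1, in a cohort that also admits 15 or more.

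**9. Crediting the baseline covariate at one visit.** The SD becomes SD × √(1 − r²). With an assumed r of 0.5, power at 70 per group is 77% (SD 5) or 53% (SD 6.7). Reaching 80% needs r of about 0.55 at SD 5 or about 0.78 at SD 6.7.

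**The case against.** The strongest reply is that the paragraph does not determine one calculation. Baseline mean and SD in days are derived here from two approximate literature figures, and the average in the SD sentence is undefined. One two-sided reading does fit: half the follow-up mean at a 20% fall gives SD 4, 92 randomised per group and 84% power at 70. This stands as a possibility, but a strained one. It applies the treated group's post-treatment spread to both groups, although the SD sentence speaks of both, and it already fails at 17.5%.

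A reader might infer that the authors simply forgot the dropout. The document does not show that. No pre-dropout number is printed, and the inference rests only on 100 matching the uninflated answer.

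A reader might also infer that the trial's power is 42–65%. That range is for an unadjusted comparison at one visit, while the planned model has a baseline covariate and two follow-ups. If the contrast were averaged over both visits under compound symmetry (an assumption; the article does not say which contrast is primary), the variance factor is (1 + r)/2 − r², at most 0.5625. Then 70 per group gives at least 88% power at SD 5 and at least 65% at SD 6.7. With a visit-specific contrast that gain is not available. This part of the reply stands: the planned analysis may do better than the unadjusted range. But the sample-size text invokes neither source of gain, so they do not explain the printed number.

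Finally, a condensed article may leave details to the full protocol. That excuses missing inputs, but not a printed conclusion that disagrees with the inputs printed beside it.

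Some simplifications favour the plan. The 2 days is a change from baseline, so any improvement in controls shrinks the contrast. Reading "almost 2" as 1.8–1.9 raises the need to about 110–123 evaluable per group even at SD 5.

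**Conclusion.** The concern holds in this form: 100 randomised per group, with 30% dropout, 5% significance and 80% power, cannot be obtained from the stated inputs on any natural reading. The shortfall is about 42 to 152 randomised per group under the baseline-mean SD, and 15 to 116 under the two milder SD readings. The calculation rests on linking the 2 days to the 15–20%, on the SD reading, and on a two-sided, unadjusted, single-visit test.

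That dropout was omitted is likely but unproven. The true power of the planned mixed model cannot be settled from the article, because it depends on a correlation and a contrast that the sample-size text does not give.

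**What to change.** Keep 200 randomised. In the sample-size paragraph of section 2.4:

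1. Delete or correct the claim that 100 per group gives 80% power after 30% dropout.
2. State the SD in days (and the mean it comes from), the sidedness, the evaluable number (200 × 0.7 = 140 in total, 70 per group) and the primary contrast: which visit, or an average of the two.
3. Restate the power or the detectable difference for that number. Either give it unadjusted, which is about 42–65% for 2 days or 2.4–3.2 days at 80% power if the SD is 5–6.7, or give it for the planned mixed model with the assumed baseline–follow-up correlation written down.

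If a different SD reading was used, stating it with the pre-dropout number would let the reader check the figure. The change costs one paragraph of wording and no additional participants. The downside is that the stated power may become less favourable.

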## 3. Expected Results

As this is a study protocol, no actual results are currently available. The following section outlines the study’s hypotheses and anticipated outcomes based on existing evidence. According to the current literature, the proposed interdisciplinary intervention, primarily based on supervised physical EXE and TPE, is hypothesized to improve clinical outcomes in individuals with MIG (e.g., frequency) and may also contribute to improvements in lifestyle-related outcomes and overall disease burden [100].

Regarding the primary outcome, the study aims to evaluate whether the intervention is associated with a reduction in MIG frequency. It is hypothesized that the intervention group may show a decrease in monthly headache days of approximately 15–20% compared with baseline [98]. This assumption is in line with previous evidence, including studies by Krøll et al. [98,99], which reported an average reduction of about two headache days per month in people engaging in PA interventions.

Regarding the secondary outcomes, in accordance with previous studies [14,17,62], we hypothesize that the intervention may be associated with improvements in MIG-related disability, MSQoL, MIG intensity, PA levels, and sedentary behavior, medication use (number of doses/month), dietary adherence, functional capacity, and postural and temporomandibular function, in line with the intervention’s interdisciplinary nature [101]. With respect to explorative measures, potential improvements may be observed in sleep quality [102], weight and WC [103,104], and key cardiometabolic parameters (including fasting glucose, HbA1c, lipid LDL, HDL, triglycerides, blood pressure, and CRP) and related risk, which may reflect changes in systemic inflammation and cardiometabolic risk, particularly among participants in the supervised EXE program [105,106]. However, these outcomes will be explored and require confirmation.

Additional benefits are anticipated in other areas, including anxiety and depression symptoms, and kinesiophobia. A reduction in allodynia scores is also hypothesized, suggesting a potential modulation of central sensitization mechanisms [107].

Although no structured nutritional intervention is planned, all participants will receive nutritional tips on EH and MIG based on guidelines to counteract the inflammatory and metabolic background of MIG, as suggested by recent literature [108]. We hypothesize that, over time, participants may show small improvements in dietary awareness, adherence to Mediterranean diet principles, and overall diet quality following the nutritional tips provided during phase 2 of the study. Particularly, participants may show greater adherence to the Mediterranean diet, higher overall diet quality (as assessed by the DRS [34]), and healthier eating behaviors, such as more regular mealtimes, improved hydration, and reduced intake of ultra-processed foods. Participants are expected to develop greater awareness of food potentially linked to an attack, although no definitive evidence supports a direct causal relationship. The use of a diary may help identify individual dietary trigger factors.

## 4. Discussion

MIG is a complex neurological disorder characterized by multifactorial etiology involving genetic, neurobiological, and environmental components [109]. Its effective management generally requires a comprehensive approach targeting modifiable risk factors to homeostasis and overall psychophysical well-being. In this context, an integrated model combining pharmacological treatment with lifestyle TPE and interventions may help reduce the burden of acute attacks and may also contribute to enhancing participants’ self-efficacy and long-term disease management, with potential benefits for quality of life. To the best of our knowledge, in recent years, relatively few studies (Table 1) have adopted a multidisciplinary approach to support individuals with MIG, and none have presented a similar, integrated model. In this context, our manuscript proposes an interdisciplinary, structured model that combines professionals’ profiles, such as neurologist, nutritionist, kinesiologist, and gnathologist profiles, in MIG management. While multidisciplinary approaches have previously been suggested, the present model intends to combine a multimodal assessment framework with these components within a single, clinically applicable model.

Given that MIG often is a social stigma for many people [110,111,112], it is imperative to focus on the role of lifestyle factors [12] and associated comorbid conditions that can exacerbate headache symptoms [112]. Specifically, according to other authors, considerations related to PA [36], nutritional aspects [113], postural alignment [114], gnathological issues [33], and psychopathological factors [115] represent potentially relevant targets to be addressed within a comprehensive management strategy. This comprehensive approach may support MIG management and contribute to a broader understanding of the multifactorial nature of headache disorders.

There is growing evidence to suggest that increased cardiometabolic risk, driven by factors such as systemic inflammation, dyslipidemia, impaired glucose metabolism, and poor diet quality, may contribute to the onset and severity of MIG. This highlights a shared pathophysiological link between metabolic health and MIG disorders from a nutritional perspective.

Elimination diets have been proposed as a strategy to identify and remove potential dietary triggers of MIG attacks; however, their overall efficacy remains modest. Although numerous foods have been implicated, convincing evidence currently supports a trigger role only for alcohol and caffeine [116]. Nonetheless, studies by Alpay et al. have explored elimination protocols based on foods associated with elevated IgG antibody levels (e.g., spices, seeds, nuts, seafood, vegetables, cheeses, fruits, and sugary products), reporting reductions in attack frequency, mean attack number, and pain intensity [37,117,118]. Nutritional strategies may benefit from being tailored to the individual’s pathophysiological profile and subsequently optimized through targeted nutrient supplementation. Certain nutrients may help prevent or ameliorate MIG by modulating oxidative stress. Given the significant variability in how individuals respond to dietary factors, keeping a food diary may help identify which foods trigger or alleviate MIG episodes [108,119]. In this context, using structured food and headache diaries and validated questionnaires could help to improve monitoring of EH and adherence to nutritional recommendations over time. Although the study does not include a standardized dietary intervention, the longitudinal collection of dietary data may help to identify behavioral patterns potentially associated with MIG frequency and severity.

According to recent studies, regular personalized PA [36] has been associated with a reduction in systemic inflammation (maybe linked to modulation of endorphin and serotonin systems), and improvement in sleep and mood. Moreover, scientific evidence shows that physical inactivity [120], poor EH [113], being overweight, and mood or sleep disorders contribute to the chronicity of the disease. Compared to previous experiences [121], this model may contribute to the ongoing development of interdisciplinary strategies for MIG management, incorporating conventional pharmacological therapies with a structured regimen of TPE and supervised EXE, while also including the assessment of EH as a non-differential component across groups [109]. Despite being relatively underexplored in the literature, some TPE experiences are starting to be documented [122,123], but to our knowledge, none of these include nutritional, neurological, posturological, gnathological, and kinesiological assessment plus supervised PA. This aspect is mainly innovative because EXE is considered a trigger by people with MIG, and they tend to avoid it [124], developing kinesiofobia [125]. Moreover, MIG pain limited PA in people who suffered [124]. The proposed model may help guide individuals with MIG toward engaging in PAs within a supervised and individualized setting, customizing the program according to postural and gnathological assessment. In fact, certain temporomandibular disorders and postural alterations can aggravate symptoms, promoting muscle tension and the activation of trigeminal nociceptive circuits [33]. Improving these aspects may contribute to reducing peripheral nociceptive inputs, preventing recurrent activation of the trigeminal-vascular system. Thanks to improved neuromuscular function and neurogenic inflammation, a reduction in allodynia and central sensitization can be expected [67].

For the previous considerations, an interdisciplinary approach, involving professionals such as neurologists, dieticians, kinesiologists, and gnathologists, allows for a more comprehensive assessment and may act on multiple aspects relevant to MIG management. This approach could promote greater treatment adherence, reducing dependence on medication and improving quality of life, laying the foundation for stable and lasting change in the lifestyle of individuals with MIG. In this context, TPE serves as a crucial resource for enhancing people’s awareness. It encourages individuals to recognize their specific triggers and fosters the development of self-management skills [126,127]. Our protocol is designed to evaluate whether a reduction of approximately 15–20% in monthly attacks and improvements in clinical metrics can be achieved. The goal is not only to achieve immediate clinical benefits but also to encourage long-lasting lifestyle changes among participants.

Additionally, our study could contribute to the development of a potentially replicable interdisciplinary model that can be applied in headache centers and in general medicine and rehabilitation settings. It also aims to promote the implementation of the EXE recommendations. However, there are potential limitations to consider.

A limitation of this study is its unblinded design, as it is impossible in behavioral intervention research like EXE. Both participants and evaluators knew group assignments, which can introduce bias and potentially overestimate the intervention’s effectiveness. Participants in the intervention group, aware of receiving active treatment and engaging regularly with a kinesiologist, may have developed heightened expectations of improvement, potentially amplifying perceived reductions in pain and quality-of-life gains beyond the actual physiological effects of EXE (enhanced placebo effect). Conversely, control group participants, conscious of not receiving active intervention, may have experienced demoralization, contributing to reduced diary compliance, higher dropout rates, or an overestimation of symptom burden (e.g., demoralization). Furthermore, given the inherently subjective nature of pain assessment, intervention group participants may have been inclined to report more favorable outcomes to justify their investment in the treatment, introducing a degree of social desirability or reporting bias. Finally, the difference between the intervention and control groups likely stems from both the actual impact of exercise and psychological effects due to the lack of blinding, which may result in a larger reported effect size than in blind studies. Moreover, it is crucial to underline that our model will be initially applied to one center (the Headache Center of Perugia). This single-headache center recruitment may limit the study’s generalizability, as participants were drawn from a single clinical site, potentially introducing selection bias. This could affect the external validity of the results, as individuals at one center may not represent the broader migraine population. Future multicenter studies with diverse participants are needed to confirm and extend these findings.

Participant adherence to both the EXE program and TPE (including nutritional tips) may vary and could potentially influence the study outcomes. To address this aspect, adherence to PA will be monitored through attendance records and wearable-device data, while EH will be observed using food-headache diaries and validated dietary tools, including the 14-item questionnaire and the DRS. These measures may help clarify the relationship between lifestyle behaviors and MIG-related outcomes. As this is a study protocol and diary data are not currently available, the diary structure and selected variables have been designed to identify behavioral patterns and potential temporal associations between EH and MIG outcomes. Recently, some authors have suggested that remote management of PA could provide benefits in this context [119,127]. The requirement for specialized personnel adds complexity to the implementation of the protocol, highlighting both its challenges and benefits, as noted by Pradelli et al. [128].

Future studies should examine how long the observed benefits last over time, as well as the effectiveness of digital or telematic interventions in supporting follow-up care.

